## 5.2 Exclusion Criteria

1. Any medical condition that in the judgement of the investigator would make the subject participation in the study unsafe.
2. Any condition, including confirmed or suspected immunosuppressive or immunodeficient condition, that in the judgement of the investigator would make it unsafe for the subject to participate.

3. History of or current autoimmune disease or impaired immune responsiveness (of any cause).
4. Having cancer or received treatment for cancer within three years (persons with a history of cancer who are disease-free without treatment for three years or more are eligible), excluding basal cell carcinoma (BCC) or squamous cell carcinoma (SCC), which are allowed unless located at the vaccination site.
5. Impaired immune responsiveness (of any cause), including diabetes mellitus.
6. Presently receiving or having a recent history of receiving (within the past six months) any medication or therapeutic modality that affects the immune system such as allergy shots, immune globulin, interferon, immunomodulators, radiation therapy, cytotoxic drugs or drugs known to be frequently associated with significant major organ toxicity, or systemic corticosteroids (oral or injectable). Inhaled and topical corticosteroids are allowed.
7. Receipt or plan to receive a non-study vaccine within 30 days prior to VX-103-01 vaccination or 60 days after vaccination.
8. Receipt of any influenza vaccine in previous 24 months and/or planned receipt of influenza vaccine through the duration of the study.
9. Diagnoses influenza infection in the previous 24 months prior to screening.
10. Diagnosed COVID infection via medical personnel or at home test within the past 60 days prior to screening.
11. Female participant who is pregnant or breastfeeding.
12. A tattoo, scar or excessive hair in volar forearm region which would impede assessment of MAP application site.
13. Allergy to influenza vaccine or components, or history of severe local or systemic reaction to any vaccination.
14. History of anaphylactic type reaction to injected vaccines
15. History of or current allergy to latex.
16. History of Guillain-Barré Syndrome.
17. Receipt of any investigational product or nonregistered drug within 30 days prior to vaccination or currently enrolled in any investigational drug study or intends to enroll in such a study within the study period.
18. Receipt of blood or blood products 8 weeks prior to vaccination or planned administration during the study period.
19. Donation of blood or blood products within 8 weeks prior to screening or at any time during the study.
20. Acute disease and/or fever ( $\geq 38.0^{\circ}\text{C}$  /  $100.4^{\circ}\text{F}$  via oral cavity) within 72 hours prior enrollment.
21. Positive test result for HBsAg, HBcAb, or HIV types 1 or 2 antibodies at screening.
22. Diagnosed eczema, atopic dermatitis or other inflammatory skin disease.
23. Significant cardiovascular disease e.g., NYHA Class 3 or 4 congestive heart failure; myocardial infarction within the past six months; unstable angina, coronary angioplasty within the past six months; uncontrolled ventricular cardiac arrhythmias; resting HR  $>100$  bpm

24. History of chronic obstructive pulmonary disease or history of other lung disease.
25. History of severe allergic reactions to eggs.
26. Use of illicit and recreational drugs throughout the trial (i.e. cocaine, amphetamines, etc.) is prohibited. The use of Marijuana is only prohibited during the 7 days prior to enrollment until after Study Day 8.
27. Diagnosis of or family history of Keloid Disease
28. History of drug or chemical abuse in the year prior to screening.
29. Consumption of alcohol for 48 hours prior to enrollment and for 24 hours after enrollment.

## 6 TREATMENT

### 6.1 Study Treatment

Details on the requirements for storage and management of study treatment, and instructions to be followed for participant numbering, dispensing, and taking study treatment are outlined in the pharmacy manual.

The MIMIX MAP application will be administered by MIMIX skin immunization to the volar forearm on Study Day 1.

All blood samples will be taken from the veins of the contralateral arm of immunization.

Refer to the ‘dietary restrictions and smoking’ [6.2.2.2 Dietary restrictions](#) for details of dosing and food intake, if relevant.

#### 6.1.1 Investigational and control product

The investigational product, VX-103 and the placebo will be prepared by Vaxess and supplied as open-labeled product to the unblinded site pharmacist ([Table 3](#)). The single use, spring-loaded applicator will be packaged and provided separately.

**Table 3: Investigational and control product**

| Investigational/
Control Product
(Name and
Strength) | Dosage Form                                                                                                                                                               | Route of
Administration     | Supply Type                     | Sponsor |
|---------------------------------------------------------------|---------------------------------------------------------------------------------------------------------------------------------------------------------------------------|--------------------------------|---------------------------------|---------|
| VX-103 7.5 µg.                                                | Microneedle array patch (MAP) with tips containing 1% silk fibroin, 0.5% Tween 20 and influenza A H1 A/Guangdong-Maonan/SWL1536/2019 CNIC-1909 antigen influenza antigens | Intradermal, skin immunization | Open label bulk supply; patches | Sponsor |
| VX-103 15 µg                                                  | Microneedle array patch (MAP) with tips containing 1% silk fibroin, 0.5% Tween 20 and influenza A H1 A/Guangdong-Maonan/SWL1536/2019 CNIC-1909 antigen influenza antigens | Intradermal, skin Immunization | Open label bulk supply; patches | Sponsor |

---

|                  |                                                                                                           |                                   |                                       |         |
|------------------|-----------------------------------------------------------------------------------------------------------|-----------------------------------|---------------------------------------|---------|
| Matching Placebo | Microneedle array patch (MAP)
with tips containing 1% silk
fibroin, 0.5% Tween 20 and no
antigen | Intradermal, skin
immunization | Open label
bulk supply;
patches | Sponsor |
|------------------|-----------------------------------------------------------------------------------------------------------|-----------------------------------|---------------------------------------|---------|

---

An unblinded pharmacist or authorized designee is required to prepare the study product.

The MIMIX MAP will be administered to the volar forearm on Study Day 1 by study personnel that have the appropriate training and are listed on the Delegation of Authority log. Prior to treatment, the forearm region of the arm must be examined, marked with indelible ink, photographed and cleaned. For the volar forearm, the site of the application must be an area of skin between ~ 4 and 8 cm below the elbow joint.

Application sites will be selected to be free from sores, scarring, blemishes, moles, tattoos, skin conditions, sunburn, heavy hair, redness or coloration which might interfere with the detection of local reactions. If possible, the non-dominant arm of the subject should be used for administration of treatment. Please refer to the VX-103-01 Instructions for Use for additional detail.

All MAP Cartridges must have been removed from 4°C storage by the Study Pharmacist and allowed to equilibrate to room temperature for at least one hour prior to opening the primary pouch, and used within 3 hours of removing from 4°C storage. Once the primary pouch has been opened the MAP must be applied within 15 minutes (+5).

MIMIX MAPs will be applied using the separate spring-powered applicator described in Section 1.2 Vaccine Design following the MIMIX MAP System use sequence shown in Figure 5 and as outlined in the Instructions for Use document Briefly, the MAP Cartridge is loaded onto the applicator by pushing the applicator directly into the open tray and between the snap hooks of the MAP Cartridge. The snap hooks are used to attach the MAP Cartridge to the applicator and to hold the Cartridge in place for MAP delivery. The loaded applicator must be held perpendicular to and just touching the skin of the application site with the arm supported.

The top of the applicator is pressed downward to apply the MAP. Following MAP deployment, the MAP Applicator and Cartridge are immediately removed from the skin, returned to the original Applicator shipping pouch, then to the original Applicator box provided by Vaxess and retained. The patch will remain on the skin for a minimum of 5 minutes and no longer than 10 minutes. The MAP is removed by study staff using gloved fingers, by gently tensioning the skin around the patch with one hand, whilst pulling the MAP directly up and away from the skin with the other hand. Following removal, the MAP should be discarded.

After the MAP has been removed, skin tolerability assessments ([Appendix 1: Local Tolerability Scoring](#)) including pain, induration, tenderness and erythema will be assessed 1 (±2), 30 (±5) and 60 (±5) minutes post-MAP removal. Other local tolerability assessments ([Appendix 2: Other Local Tolerability Scoring](#)) including bruising, itching, skin-flaking and pigmented coloration will be assessed 60 (±5) minutes post-MAP removal.

If erythema, bruising or induration  $\geq 1$  cm around the treatment site is present, the maximum diameter will be recorded.

The MAP application site will be photographed with the study specific iPhone 1 ( $\pm 2$ ), 30 ( $\pm 5$ ) and 60 ( $\pm 5$ ) minutes post-MAP removal and with the iPhone attached to the study specific DermLite Imaging system 60 ( $\pm 5$ ) minutes post-MAP removal. Please refer to the Imaging Instructions document for additional details.

During the follow up visits, tolerability assessments, photographs of the MAP application site and blood samples will be taken for safety and immunogenicity assessments per the Assessment Schedule [Table 5](#).

**Figure 5: MIMIX MAP System Use Steps**

[figure not shown]

### 6.1.2 Additional Study Treatments

No other treatment beyond investigational drug and control are included in this trial.

### 6.1.3 Treatment Arms/Groups

Participants will be randomized at Day 1 to one of the following “n” treatment arms/groups. The participants will be randomized in a 1:1:1 manner.

Approximately 45 healthy adult participants will be enrolled in the study.

The planned doses are the following:

- Group 1: 15 µg
- Group 2: 7.5 µg
- Group 3: Placebo

## **6.2 Other Treatments**

### **6.2.1 Concomitant Therapy**

Concomitant therapy for intercurrent medical events should be discussed between the sponsor and the investigator or his designee.

Approved killed, inactivated, peptide, deoxyribonucleic acid and ribonucleic acid (RNA) vaccines may be permitted 30 days prior to VX-103 dosing or 60 days after VX-103 dosing according to the investigator's discretion and per local guidance. All medications, procedures, and significant non-drug therapies (including physical therapy) administered after the participant was enrolled into the study must be recorded on the appropriate electronic case report form (eCRF).

Each concomitant drug must be individually assessed against all exclusion criteria/prohibited medication. If in doubt, the investigator should contact the Sponsor's medical monitor or designee before randomizing a participant or allowing a new medication to be started. If the participant is already enrolled, contact Vaxess or designee to determine if the participant should continue participation in the study.

### **6.2.2 Restriction for study participants**

For the duration of the study, participants should be informed and reminded of the restrictions outlined in this section.

#### **6.2.2.1 Restrictions to prevent pregnancy**

Non-clinical reproductive toxicity studies have not yet been performed to date with VX-103. It is unknown if there is any potential impact on a pregnancy by VX-103. Therefore, sexually active males and females participating in this clinical trial are required to use highly effective contraception methods.

The following highly effective methods of contraception are accepted:

- Established use of oral, intravaginal, or transdermal combined (estrogen and progestogen containing) hormonal contraception associated with inhibition of ovulation.
- Established use of oral, injectable, or implantable progestogen-only hormonal contraception associated with inhibition of ovulation.
- Placement of an intrauterine device (IUD) or intrauterine hormone-releasing system (IUS).
- Barrier methods of contraception: male condom with either cap, diaphragm or sponge with spermicide (double barrier methods). The use of double barrier methods should always be supplemented with the use of a spermicide. Female condom and male condom should not be used together.
- Male sterilization (provided that the partner is the sole sexual partner of the patient and that the sterilized partner has received medical assessment of the surgical success.)

- Sexual abstinence

#### **6.2.2.2 Dietary restrictions**

1. No alcohol for 48 hours prior to enrollment and for 24 hours after Day 1.
2. The use of recreational Marijuana is only prohibited during the 7 days prior to enrollment until after Study Day 8.

### **6.3 Participant numbering, treatment assignment, randomization**

#### **6.3.1 Participant numbering**

Each participant is identified in the study by a Participant Number (Participant No.) that is assigned when the participant is enrolled for screening and is updated for the participant upon enrollment in the trial. The Participant No. consists of the Site Number (Site No.) (as assigned by Vaxess or designee to the investigative site) with a sequential participant number suffixed to it, so that each participant's participation is numbered uniquely across the entire database. Upon signing the informed consent form, the participant is assigned to the next sequential Participant No. available.

#### **6.3.2 Treatment assignment, randomization**

A randomization list will be produced by Icon by following their internal process using a validated system that automates the random assignment of treatment arms to randomization numbers in the specified ratio.

The randomization scheme for participants will be reviewed by the study biostatistician.

### **6.4 Treatment blinding**

All groups are unblinded except the rater and subject who will remain blinded to study treatment throughout the study, except where indicated below.

The identity of the treatments will be concealed by the use of study vaccines that are all identical in packaging, labeling, schedule of administration, appearance, and odor.

#### **Site staff**

All site staff that have been delegated as a rater on the Delegation of Authority log will be blinded to study treatment during treatment allocation and participant dosing.

Unblinding a single participant at site for safety reasons (necessary for participant management) will occur via an emergency system in place at the site.

The unblinded pharmacy staff will receive a randomization list or treatment allocation information from Vaxess or designee with the appropriate treatment allocation numbers. Appropriate measures must be taken by the unblinded pharmacist to ensure that the treatment assignments are concealed from the blinded site staff.

#### **Sponsor staff**

The following unblinded sponsor roles are required for this study:

- Unblinded clinical staff managing drug re-supply to site
- Blinded sample analyst(s) (immunogenicity)

The monitors are not provided with a randomization list directly but will be unblinded through review of source documentation compiled by the unblinded pharmacist or designee, which details treatment allocation to individual participants. The monitors will also be able to review the treatment allocation information/randomization list provided to the unblinded pharmacist. The name(s) of the monitor(s) are detailed in the monitoring plan, if applicable.

Sponsor or designee clinical staff are required to assist in the management and re-supply of investigational drug product. These individuals are not provided with randomization lists directly but may be unblinded through communication of drug re-supply needs via the unblinded site pharmacists.

The sample analysts will receive a copy of the randomization schedule to facilitate analysis of the samples. The sample analysts will provide the sample data to the study team under blinded conditions unless otherwise allowed.

The study statistician will be able to access the full randomization list from the start of the study and is allowed to share unblinded information with the rest of the clinical trial team as appropriate for internal decision purposes, as outlined in [Table 4](#). For example, unblinded summaries and unblinded individual data can be shared with the team whenever necessary.

Study programmers and other personnel involved in study data analysis (e.g. immunogenicity expert) are allowed to access treatment assignment information from the start of the study for the purpose of data analysis.

The Vaxess clinical trial team is allowed to share unblinded results with other sponsor staff (e.g. decision boards) as required for internal decision making on the study or the project while the study is ongoing.

All unblinded personnel will otherwise keep randomization lists and data or information that could unblind other study team members confidential and secure except as described above.

Following final database lock, all roles may be considered unblinded.

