## 4 RATIONALE

### 4.1 Rationale for study design

This is a standard FIH study design. The study will use a rater and participant-blinding, a placebo-controlled design and a single dose regimen.

- **Healthy participants:** The absence of co-morbid disease in healthy participants allows for an unbiased assessment of the safety and tolerability
- **Blinding:** Blinding allows for an unbiased assessment of readouts such as adverse events
- **Dietary restrictions:** Food restriction from at least 4 hours prior to dosing until after completion of the post dose assessments is implemented to avoid effects of food on assessments.
- **Randomization:** Will be performed via a randomization plan. This decreases the chance of an imbalance in participant characteristics between groups, thereby facilitating and unbiased assessment of safety, reactogenicity and tolerability
- **Inpatient for dosing:** This allows for close observation of safety, reactogenicity and tolerability, and ensures compliance with instructions for all participants.

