**Table 4: Blinding and Unblinding Plan**

| Role                                                                                                                          | Randomization list generated | Treatment allocation & dosing | Safety event (single participant unblinded) |
|-------------------------------------------------------------------------------------------------------------------------------|------------------------------|-------------------------------|---------------------------------------------|
| Participants                                                                                                                  | B                            | B                             | UI                                          |
| Rater Only staff                                                                                                              | B                            | B                             | UI                                          |
| Unblinded site staff e.g. pharmacy staff and data entry                                                                       | B                            | UI                            | UI                                          |
| Vaccine Clinical Supply and Randomization                                                                                     | UI                           | UI                            | UI                                          |
| Unblinded sponsor staff or designee e.g. for study treatment resupply, unblinded monitor(s), sample analyst(s)                | B                            | UI                            | UI                                          |
| Unblinded Pharmacovigilance sponsor staff or designee                                                                         | B                            | UI                            | UI                                          |
| Statistician/statistical programmer/ data analysts (e.g. immunogenicity)                                                      | B                            | UI                            | UI                                          |
| All other sponsor staff not identified above (i.e. trial team, project team, management & decision boards, support functions) | B                            | UI                            | UI                                          |

Key:

UI: Allowed to be unblinded on individual participant level

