| Medical Questioning                                                   | The investigator will assess the participant for any reported AEs and ensure approval is provided before discharging the participant from the site.                                                                                                                                                                                                                                                                                                                                                                                                                                                                                                                                                                                                                                                      |

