#### **8.5 Additional assessments**

##### **8.5.1 Immunogenicity**

To describe the immunogenicity of VX-103, serum samples for determination of HAI antibodies will be collected at the time points defined in the Assessment Schedule ([Table 5](#)).

HAI titers, virus microneutralization titers, anti-HA, anti-fibroin IgG and total IgE will be assessed in serum of all participants, including the placebo group.

Instructions are outlined in the lab manual regarding tube handling, sample collection, numbering, processing, and shipment. In order to better define immunogenicity, the timing of the serum sample collection may be altered based on emergent data.

Serum samples remaining after completion of analysis may be used for exploratory assessment or other bioanalytical purpose (e.g., other bioanalytical exploratory assessments).

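### Assay analysts called blinded are given the randomization schedule, and the protocol lets an unblinded investigator judge AE causality because it assigns the investigator no blinding status

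*Protocol*

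**What the plan says.** **Assay analysts.** The Sponsor staff part of section 6.4 opens a list with "The following unblinded sponsor roles are required for this study", and one entry is "Blinded sample analyst(s) (immunogenicity)". Further down it states: "The sample analysts will receive a copy of the randomization schedule to facilitate analysis of the samples". The sentence after that has the analysts pass their data to the study team blinded, unless otherwise allowed. Table 4 groups them with unblinded sponsor staff ("unblinded monitor(s), sample analyst(s)"). That row is B when the list is generated and UI, meaning individual unblinding is allowed, from treatment allocation and dosing onward. Section 8.5.1 says that HAI, microneutralization, anti-HA, anti-fibroin IgG and total IgE "will be assessed in serum of all participants, including the placebo group".

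**Site staff.** Section 6.4 sets the default: "All groups are unblinded except the rater and subject who will remain blinded to study treatment throughout the study, except where indicated below". Its Site staff part applies blinding to those delegated as raters. Section 6.6.3 repeats that only rater and subject are blinded and, for that reason, keeps the randomization list at the site. On AEs, Table 6 says "The investigator will assess the participant for any reported AEs", and section 10.1.1 makes the investigator responsible for identifying AEs and requires a relationship to treatment for each one. Section 4.1 gives the purpose: "Blinding allows for an unbiased assessment of readouts such as adverse events".

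**The concern.** The laboratory cannot follow all of section 6.4 at once, because it is told that its analysts are blinded and also that they hold the allocation. If they do hold it, the HAI titres behind the secondary immunogenicity endpoints in Table 1 (geometric mean titre, fold rise, seroconversion) can be read by someone who knows the arm. Section 12.1 also builds the immunogenicity set on measurements not flagged for exclusion and on deviations judged to affect the data, and it does not require those decisions to be made blind.

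On the clinical side, relatedness and attribution to vaccination are judgements. Section 4.1 relies on blinding to keep AE assessment unbiased, but the operative text protects only people named as raters and never says that whoever attributes an AE must be one. A titre read or a causality call made with the allocation known cannot be re-blinded later, so this has to be settled before data are generated.

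**Working it through.** The plan states no figure to reproduce. The sample size in section 12.8 rests on precedent, without alpha, power or effect size. The check compares the text on who may know allocation and when.

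**Assay analysts**
1. Four statements in section 6.4 bear on their status. The list heading says unblinded, the list entry says blinded, the later sentence hands over the randomization schedule, and Table 4 says UI from dosing. Three of the four agree on unblinded.
2. Need: sections 8.3 and 8.5.1 have samples from all participants, placebo included, evaluated. Nothing makes an assay depend on the arm, so no documented step needs the schedule.
3. Safeguard: the blinded-conditions sentence governs release of data to the study team. It does not govern reading the assay.
4. Consequence: titres, and any validity flags the analysts set, can be generated with allocation known. Section 12.1 does not say who sets the flags.

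**AE attribution**
1. Of the eight roles in Table 4, six are UI at treatment allocation and dosing. Only participants and rater-only staff are B. The investigator has no row.
2. 'Rater' is not defined, and no section requires the investigator to be delegated as one.
3. In section 9.1.4, five of the seven stopping-rule rows depend on the event not being reasonably attributable to a cause other than vaccination: any SAE; withdrawal after a grade 3 AE; solicited AE with hospitalization or high fever; prolonged grade 3 solicited general AE; grade 3 unsolicited AE or laboratory abnormality.
4. Section 12.4.2 gives related AEs a separate summary, so relatedness enters the primary safety reporting directly.

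**Sensitivity only**
- Assume a fraction x of one arm's reads moves by one two-fold dilution. The geometric mean titre then shifts by a factor of 2^x: 2^0.2 = 1.15 at x = 20%, and 2^0.5 = 1.41 at x = 50%. Both values of x are assumptions, and the protocol supports neither.
- With 15 per arm (Table 2), one participant moved across the four-fold or 1:40 line changes that arm's rate by 1/15 = 6.7 percentage points.
- If both active arms shifted equally, the 7.5 µg to 15 µg titre ratio would not change. The contrast with placebo and the absolute rates would.

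**The case against.** **The word 'blinded' may be a slip.** The other three statements agree, and the study title promises only rater and participant blinding. Read so, the contradiction is editorial. That is fair, but it leaves analysts holding the allocation while they generate titres, with no stated reason.

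**The mechanism is partly outside the document.** The protocol describes neither repeat reads nor subjective reading, and sample numbering is left to the lab manual, which may require coded tubes. This stands as a limit on the claim. Coded tubes would not cancel a sentence that gives analysts the schedule.

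**The investigator may be blinded in practice.** Section 6.4 has the pharmacist conceal assignments from blinded site staff. The code-break procedure in section 6.6.3, for which the investigator is responsible, fits poorly with an investigator who already knows the arm. This stands too: the defect is an undefined status that permits either arrangement.

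**Stronger readings a reader might infer.**
- That titres or causality calls will be biased. The text shows only that knowing the allocation is permitted.
- That every antibody endpoint is exposed alike. The concern here is with HAI and microneutralization titres. ELISA is named for other exploratory assays, and no reading mechanism has been shown for those.
- That the primary endpoint as a whole is compromised. Section 12.4.1 counts all safety data as primary: vital signs, laboratory values, examinations, AEs and reactogenicity. AE incidence needs no attribution, tolerability scored by delegated raters stays blinded, and itching and flaking come from blinded participants.
- That almost nobody should hold the allocation. Three stopping-rule rows apply in an investigational group, and section 12.7 plans an interim analysis, so some staff outside the site need it.

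**Conclusion.** The point holds in two parts of unequal strength.

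The analyst part is explicit and held with high confidence. Their stated status is contradictory, their access to allocation has no documented purpose, and the one safeguard acts after the titre has been read. The exposure covers HAI and microneutralization titres and any exclusion flags the analysts set.

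The investigator part is held with moderate confidence because it rests on a default rule plus silence. The protocol permits an unblinded investigator to judge relatedness and the attribution in five of seven stopping-rule rows, which the aim in section 4.1 does not allow for. It does not state that the investigator is unblinded.

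The size of any bias cannot be derived from the protocol. The 1.15- to 1.41-fold range is a what-if under assumed shifts; the 6.7 points is arithmetic for one reclassified participant in an arm of 15. In an exploratory first-in-human study with a descriptive primary objective, this is a should-fix.

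**What to change.** **Analysts.** In section 6.4, delete the sentence that gives them the schedule and take them out of the list of unblinded roles. In Table 4, separate them from the unblinded sponsor staff and show B until assay results and validity flags are locked. Send sera under coded identifiers, and say so in the lab manual. State in section 12.1 that exclusions from the immunogenicity set are decided without reference to allocation.

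**Investigator.** Define 'rater', add an investigator row to Table 4, and state in section 6.4 that site staff who grade AEs or judge their causality are blinded raters. The emergency code-break route in section 6.6.3 already serves when the allocation is needed.

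**Leave as is.** Allocation access for supply, pharmacovigilance and statistics staff should stay. Attribution can then be judged blind at the site, and group membership applied by someone who already holds the list.

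**Cost.** Text edits to sections 6.4 and 12.1, Table 4 and the lab manual. An unblinded pharmacist and an unblinded administrator are already foreseen. The protocol gives no site staffing, and Table 4 counts data entry among unblinded site staff, so a small site may have to keep data entry apart from AE grading. A blinded investigator must also use the code-break route instead of consulting the list.
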